## Study procedures

Study procedures are outlined in table 2.

**Table 2 T2:** Summary of procedures in observational cohort

Assessment	Hospitalisation		Post discharge*				
	Baseline†	Discharge‡	2 weeks	4 weeks	12 weeks	24 weeks	48 weeks
Caregiver informed consent to join observational cohort	x						
Summary checklist	x						
Locator information§	x						
Acute admission information	x						
Baseline data	x						
Daily clinical review¶	Daily during hospitalisation						
Blood collection**	x	x			x	x	x
HIV testing††	x						
CD4 count and viral load (HIV-infected children only)	x				x	x	x
Full blood count‡‡	x	x			x	x	x
Anthropometry	x	x	x	x	x	x	x
Skinfold thickness§§		x	x	x	x	x	x
Body composition¶¶	x	x	x	x	x	x	x
Discharge data collection		x					
Daily morbidity diary			Daily during follow-up period by caregivers				
Follow-up clinic: history, examination, morbidity and mortality data			x	x	x	x	x

*Windows will be created around these post-discharge time-points to maximize follow-up for caregivers who miss visits or are unavailable, as follows: 2 weeks (optimal window from 1 week to 2 weeks + 6 days; allowable window up to 2 weeks + 6 days); 4 weeks (optimal window 3-5 weeks, allowable window up to 9 weeks + 6 days); 12 weeks (optimal window 10-14 weeks, allowable window up to 19 weeks + 6 days); 24 weeks (optimal window 20-28 weeks, allowable window up to 43 weeks + 6 days); 48 weeks (optimal window 44-52 weeks, allowable window up to 71 weeks + 6 days). †Children will be enrolled as soon as possible after hospitalisation and will undergo baseline investigations as soon as possible after enrolment. This is to provide a window of opportunity to time collection of research specimens with clinical specimens, and to ensure that the child is clinically stable before undertaking research investigations.

‡The discharge procedures will be undertaken on the day of discharge or as close as possible to that date.

§Locator information will be updated at subsequent visits if caregivers have moved or changed contact details.

¶A clinical review will be undertaken every day between admission and discharge by the study clinician.

**5.4 mL of blood (depending on child weight; amount will not exceed 2 mL/kg total over 2-week period) will be collected by a study nurse into endotoxin-free EDTA tubes. Samples will be used to store whole blood, Peripheral Blood Mononuclear Cells (PBMC) and plasma for subsequent measurement of C reactive protein and albumin. Where blood sample volumes allow (≥2 mL sample), bacterial binding assays and whole blood stimulations will be conducted and culture supernatants and cells stored for subsequent assessment of immune cell function at each time point. Study blood samples will not be collected from children with known haemoglobin <60g/L.

††HIV testing is conducted as part of routine clinical practice, but if it has not been undertaken, the study sample will be used to test for HIV, as stated in the informed consent form, since HIV status is required to allocate children to study groups.

‡‡Full blood count results will be transcribed from clinical records; if not done by clinical teams, the EDTA sample will be used to measure Full Blood Count (FBC) in clinical laboratories at each site.

§§Skinfold thickness (triceps, subscapular, supra-iliac) and mid-thigh circumference will be measured using Holtain callipers or tape measure.

¶¶Body composition will be assessed by bioimpedance vector analysis.

### Baseline procedures

Baseline data on maternal and household characteristics, the child’s medical history and current illness are collected by a study nurse. Anthropometry, including body composition measured by whole-body (wrist-ankle) bio-electrical impedance analysis (BodyStat 1500MD; BodyStat, UK), leg length using an electronic knemometer (Zimbabwe only, due to availability of knemometers) and triceps, subscapular and supra-iliac skinfold thickness using callipers (Holtain, Crymych, UK), are undertaken at baseline. Blood (1 mL/kg up to 5.4 mL maximum) is collected at baseline into an endotoxin-free EDTA tube for all children and, in the enteropathy substudy, additionally into a PAXgene tube (PreAnalytiX, Hombrechtikon, Switzerland) for subsequent transcriptomic analysis. Blood is not collected from children with severe anaemia (known haemoglobin <60 g/L). HIV testing is carried out in accordance with national guidelines as part of routine clinical practice; where it has not been done, the child’s HIV status is ascertained using a rapid test antibody algorithm for children over 18 months, or HIV DNA PCR for children under 18 months. CD4 count/percentage and viral load are measured in HIV-positive children. Maternal HIV status is documented where available, so that HIV-exposed uninfected children can be identified. Blood samples are sent to research laboratories at each site to conduct whole blood stimulation and bacterial binding assays (as described in the immunology substudy) and to store aliquots of whole blood, peripheral blood cells and plasma at −80⁰C.^31^ In the enteropathy substudy, nasogastric aspirate, stool and urine (after an oral dose of lactulose and mannitol) are also collected. Lactulose and mannitol are ingested by the child after fasting and urine is collected over a 2-hour period to measure recovery of lactulose and mannitol, a measure of intestinal absorptive capacity and permeability, as previously described.^32^

### Daily procedures

Routine inpatient management is undertaken by ward clinical teams according to local hospital protocols, which are based on WHO guidelines.^2^
^33^ In addition, the HOPE-SAM study clinician at each hospital site collects daily data until discharge on clinical parameters (including daily examination), resolution of acute infections, nutritional recovery (loss of oedema, restoration of appetite, weight gain) and treatment/nutritional supplements received; this will allow us to evaluate differences in management between countries. Children with HIV-SAM who are ART-naive start ART according to national guidelines, which are based on WHO recommendations.^2 34^

### Discharge

The clinical team decides when the child is ready to be discharged, which is generally when their medical complications are resolving and the child has a good appetite and is clinically well and alert.^2^ Children receive ready-to-use therapeutic feeds (RUTF) to take at home according to local guidelines. At discharge, the study nurse collects data and a repeat blood sample (including full blood count) and undertakes discharge anthropometry, body composition, leg length (Zimbabwe only) and triceps, subscapular and supra-iliac skinfold thickness measurements (table 2). The caregiver is given a daily morbidity diary and pre-prepared stickers corresponding to different illnesses and shown how to complete the diary. The caregiver is provided with the date of the first follow-up appointment and contact details of the study nurse.

### Follow-up

Children attend follow-up appointments at dedicated study clinics at 2, 4, 12, 24 and 48 weeks post discharge. At each visit, the study physician undertakes a clinical assessment and the study nurse captures illness, medication and feeding data. Clinic data are transcribed from handheld medical records if available and the morbidity diary is reviewed and a new diary and stickers supplied. Anthropometry, body composition, leg length (Zimbabwe only) and triceps, subscapular and supra-iliac skinfold thicknesses are measured at each visit. Acute illnesses are treated in the study clinic or the child is referred to hospital if necessary. Children with relapsed malnutrition are provided with nutritional supplements or RUTF according to local guidelines or readmitted to hospital if they develop complicated SAM. Transport reimbursement for clinic attendance is provided to caregivers for each visit.

Blood is collected at weeks 12, 24 and 48 post discharge into endotoxin-free EDTA tubes to measure full blood count, CD4 count and viral load (HIV-positive children only), conduct whole blood stimulation and bacterial binding assays (where blood volumes > 2 mL) and store peripheral blood cells and plasma aliquots for subsequent analyses (all blood samples), including soluble and cellular markers of immune activation, as outlined in online supplementary table 1. Children in the enteropathy substudy have additional stool and urine collection following lactulose-mannitol dosing as shown in table 3.

10.1136/bmjopen-2018-023077.supp1Supplementary data

**Table 3 T3:** Summary of procedures for cases in the enteropathy substudy

Assessment	Hospitalisation		Post discharge*				
	Baseline†	Discharge‡	2 weeks	4 weeks	12 weeks	24 weeks	48 weeks
Caregiver informed consent to join observational cohort and enteropathy substudy	X						
Summary checklist	X						
Locator information§	X						
Acute admission information	X						
Baseline data	X						
Daily clinical review¶	Daily during hospitalisation						
Blood collection**	X	X			X	X	X
HIV testing††	X						
CD4 count and viral load (HIV-infected children only)	X				X	X	X
Full blood count‡‡	X	X			X	X	X
Gastric aspirate§§	X						
Stool collection¶¶	X	X			X	X	X
Lactulose-mannitol testing***	X	X			X		X
Anthropometry	X	X	X	X	X	X	X
Skinfold thickness†††		X	X	X	X	X	X
Body composition‡‡‡	X	X	X	X	X	X	X
Discharge data collection		X					
Daily morbidity diary			Daily during follow-up period by caregivers				
Follow-up clinic: history, examination, morbidity and mortality data			X		X	X	X

*Windows will be created around these post-discharge time points to maximise follow-up for caregivers who miss visits or are unavailable, as follows: 2 weeks (1–3 weeks); 4 weeks (3–5 weeks); 12 weeks (10–14 weeks); 24 weeks (20–28 weeks) and 48 weeks (44–52 weeks).

†Children will be enrolled within 24 hours of hospitalisation and will undergo baseline investigations within 72 hours of hospitalisation. This is to provide a window of opportunity to time collection of research specimens with clinical specimens, and to ensure that the child is clinically stable before undertaking research investigations.

‡The discharge procedures will be undertaken on the day of discharge or as close as possible to that date.

§Locator information will updated at subsequent visits if caregivers have moved or changed contact details.

¶Daily clinical review will be conducted every day between admission and discharge by the study clinician.

**During hospitalisation, 5.4 mL of blood (depending on child weight; amount will not exceed 2 mL/kg total over 2-week period) will be collected by a study nurse into a 2.7 mL endotoxin-free EDTA tube and a 2.7 mL PAXGene tube, for subsequent isolation of RNA and gene expression analysis. After discharge (weeks 12, 24 and 48), 5.4 mL of blood (depending on child weight; amount will not exceed 2 mL/kg total over 2-week period) will be collected by a study nurse into two 2.7 mL endotoxin-free EDTA tubes.

††HIV testing is conducted as part of routine clinical practice, but if it has not been undertaken, the study sample will be used to test for HIV (see section 9.4), as stated in the informed consent form, since HIV status is required to allocate children to study groups.

‡‡Full blood count results will be transcribed from clinical records; if not done by clinical teams, the EDTA sample will be used to measure FBC in clinical laboratories at each site.

§§A gastric juice sample will be collected at the same time as the blood draw by aspirating the nasogastric tube with a sterile feeding syringe, to test for gastric pH; sterile water or saline will then be instilled and a sample of gastric juice collected for storage for subsequent PCR and culture (section 7.5.2).

¶¶Stool collection will be undertaken at the same time as the blood draw.

***Lactulose-mannitol (LM) testing will be conducted, with collection of a baseline urine sample, followed by a 2-hour urine collection post-LM ingestion. This test will be deferred until children are judged to be clinically stable by the study physician during daily reviews. In general, this will be a child in the nutritional rehabilitation phase, who has no cardiorespiratory compromise.

†††Skinfold thickness (triceps, subscapular, supra-iliac) and mid-thigh circumference will be measured using Holtain callipers or tape measure.

‡‡‡Body composition will be assessed by bioimpedance vector analysis.

Caregivers are reminded of follow-up visits by phone, and visit completion is tracked on a dedicated database. If caregivers do not attend follow-up appointments, attempts are made to contact them by phone and home visits are made if feasible, particularly for those defaulting on the 48-week visit, so that long-term outcome data can be collected. For post discharge deaths, a home visit is undertaken by study nurses where possible to conduct a verbal autopsy. Children who are readmitted to one of the study sites with relapsed SAM have data collected during the new episode of hospitalisation. The study ends for each participant at the week 48 visit.

## Substudies

As outlined in figure 1, four nested substudies will use biological specimens to address mechanistic questions related to enteropathy, microbiota, metabolomics and immune function.

### Enteropathy substudy

The gut, which acts as an internal interface between humans and the environment, must contain the nutrient stream and the symbiotic microbiota while allowing molecular intimacy to permit absorption. The mechanism underlying this duality is the integrity of the gastrointestinal barrier; intestinal damage (enteropathy) can impair this critical barrier function. A spectrum of enteropathies affect children in developing countries.^30^ Environmental enteric dysfunction (EED), characterised by small intestinal inflammation, blunted villi and increased intestinal permeability, is almost universal and is morphologically indistinguishable from HIV enteropathy.^30^ Children in resource-poor settings also suffer from frequent diarrhoea, food insecurity and micronutrient deficiencies, which all exacerbate enteropathy.^30^ As a result, a cycle of intestinal infection, impaired mucosal function and malnutrition commonly arises, which may ultimately precipitate SAM, especially in the context of HIV infection.^35 36^ It is not yet established if the enteropathy seen in children with SAM,^37^ which we here refer to as malnutrition enteropathy,^37^ is qualitatively or quantitatively distinguishable from EED. In addition to local intestinal pathology, enteropathies may cause systemic pathology due to persistent immune activation arising from enteric inflammation and microbial translocation across the damaged gut wall.^30^ It is becoming apparent that chronic inflammation may be particularly deleterious in malnourished individuals^23^; in children with SAM, systemic inflammation arising from underlying enteropathy may further increase morbidity and mortality.

We hypothesise that (i) the degree of enteropathy during hospitalisation differs between oedematous and non-oedematous SAM and is independently associated with morbidity, mortality and nutritional recovery during hospitalisation; (ii) the degree of enteropathy at discharge is independently associated with morbidity, mortality and relapse of SAM; and (iii) children with HIV-SAM have more severe enteropathy than HIV-negative children with SAM, which contributes to their poorer outcomes.

Using stored samples, a longitudinal series of investigations will compare gastric and small intestinal barrier function, using a range of biomarkers to capture the domains of malnutrition enteropathy (online supplementary table 2). To understand better the extra-intestinal consequences of enteropathy, we will first compare the microbial composition of the upper gut and plasma using deep sequencing in a subgroup of children with paired gastric and blood samples. Second, we will undertake transcriptomics using PAXGene blood samples to determine (i) whether there are differences in gene expression profiles between well-nourished controls, HIV-negative children with SAM and HIV-positive children with SAM (including comparison of oedematous and non-oedematous types); and (ii) whether specific patterns of gene expression are associated with morbidity and mortality in SAM.

### Microbiota substudy

Normal assembly of the gut microbiota in early life is critical for many aspects of physiological, neurological and immune development.^38^ Recent evidence suggests that an immature or pathogenic microbiota plays a causative role in the pathogenesis of SAM.^25^ For example, a number of microbial taxa have been identified, including *Faecalibacterium prausnitzii*, which discriminate and predict gut microbiota maturity and child growth.^28^ Other pathogenic microorganisms, including IgA-targeted *Enterobacteriaceae*, are associated with impaired growth and may contribute to SAM.^39^ Nutritional rehabilitation with RUTF induces temporary recovery of a disturbed microbiota; however, the microbiota appears to revert back to an immature diseased state following nutritional recovery.^29^ HIV infection is also associated with a disturbed gut microbiota,^40^ which may further compound enteropathy phenotypes. Furthermore, there is some evidence that differences exist in malnutrition enteropathy between oedematous and non-oedematous SAM^41^; however, few studies have investigated differences in the gut microbiota between the two forms of the disease.

We hypothesise that (i) a unique gut microbial signature exists in HIV-SAM, compared with HIV-negative children with SAM, that is independently associated with morbidity, mortality, nutritional recovery and degree of enteropathy during hospitalisation; (ii) a unique gut microbial signature exists in oedematous compared with non-oedematous SAM; (iii) specific microorganisms or gut microbial diversity indices are independently associated with morbidity, mortality, nutritional recovery and degree of enteropathy during hospitalisation; and (iv) the gut microbiota is partially restored to a healthy state with nutritional rehabilitation but reverts to a dysbiotic state during follow-up, which predicts morbidity, mortality and relapse of SAM.

Using stored stool samples collected at baseline, a cross-sectional investigation will determine differences in the gut microbial composition and predicted function between: HIV-negative children with SAM versus HIV-SAM, oedematous versus non-oedematous SAM and well-nourished controls. Gut microbial composition and predicted function will be compared between groups at discharge and at 12, 24 and 48 weeks post discharge. Briefly, total DNA and/or RNA will be extracted from stool samples and used as template for next-generation sequencing library preparation and for quantitative PCR. Whole metagenome shotgun sequencing will be performed using the HiSeq 2500 system. Raw metagenomic sequencing data will be quality-filtered and analysed through a well-validated bioinformatics pipeline using MetaPhlAn^42^ and HUMAnN.^43^ The compositional and predicted functional metagenomic data generated will be used to identify signatures of SAM and to investigate associative links between specific gut microbial signatures and clinical outcomes.

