## Introduction

Malnutrition underlies almost half of all childhood deaths in developing countries.^1^ Severe acute malnutrition (SAM) is defined by a weight-for-height Z-score (WHZ) <–3, mid-upper arm circumference (MUAC) <115 mm and/or bilateral pitting oedema.^2^ Current treatment guidelines distinguish two groups: (i) children with uncomplicated SAM who can be managed in the community and (ii) children with complicated SAM, who are hospitalised and undergo resuscitation, stabilisation and nutritional rehabilitation. In-hospital mortality in children with complicated SAM remains high despite the implementation of WHO guidelines.^3^ Furthermore, SAM presents as two major clinical phenotypes: non-oedematous SAM (marasmus), characterised by severe wasting, and oedematous SAM (kwashiorkor), a more complex syndrome characterised by bilateral pitting oedema, steatosis and diarrhoea.^4 5^ Despite differing clinical outcomes, treatment protocols are the same for both oedematous and non-oedematous SAM.

A contributory factor to high inpatient mortality is the co-occurrence of HIV infection in around one-third of children hospitalised for SAM in sub-Saharan Africa.^6 7^ While new HIV infections in children have declined,^8^ a substantial number of infected children are diagnosed late and present with malnutrition. There is also a growing population of HIV-exposed uninfected (HEU) children who have immune abnormalities, poor growth and higher risk of mortality and infectious morbidity.^9^ Hence, HIV has transformed the epidemiology and outcomes of SAM.^10^ Even with standardised treatment approaches, inpatient deaths are almost fourfold higher among HIV-positive children with SAM (herein termed HIV-SAM) compared with HIV-negative children with SAM (30.4% vs 8.4%), for reasons that remain unclear^10^; this mortality is threefold higher than would be expected from anthropometric parameters alone.^10^ Management of HIV-SAM is particularly challenging because HIV fundamentally alters the clinical presentation of malnutrition and the response to treatment. Children with HIV-SAM are more stunted and wasted; have a higher frequency of persistent diarrhoea; tend to have delayed nutritional recovery and have a more complicated clinical course than HIV-negative children with SAM.^10^

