### Metabolomics substudy

During SAM, metabolic processes are altered in response to a starved environment and may plausibly contribute to long-term clinical outcomes. Previous studies suggest that amino acid turnover, lipid metabolism, oxidative stress and other metabolic pathways are disrupted in SAM and may be associated with disease state and clinical outcome^26 44 45^; however, little is known about how the metabolic phenotype responds to nutritional therapy. It is hypothesised that disturbed gut microbiota composition and function may drive microbial metabolic dysregulation in addition to host-derived dysregulation. Of particular interest are differences in the metabolic phenotype between oedematous and non-oedematous SAM. The ‘reductive adaptation’ seen in non-oedematous SAM (utilisation of fat and muscle stores) is disrupted in oedematous SAM, which may contribute to differences in clinical outcomes. Specifically, protein turnover, inflammation, oxidative stress and bile acid metabolism are disrupted in oedematous-SAM, which may contribute to comorbidities including diarrhoea, steatosis and enteropathy.^46 47^

We hypothesise that (i) a unique plasma and urine metabolic phenotype exists in oedematous compared with non-oedematous SAM during hospitalisation, which is independently associated with morbidity, mortality and nutritional recovery; (ii) the metabolic phenotype is partially restored to a healthy state with nutritional rehabilitation but reverts to a disturbed state during follow-up, which predicts morbidity, mortality and relapse; and (iii) both host-derived and gut microbial-driven metabolic dysregulation underlie clinical outcomes.

Using stored urine and plasma samples collected during hospitalisation, a cross-sectional investigation will determine differences in the metabolic phenotype between children with oedematous SAM, non-oedematous SAM and well-nourished controls. Urine and plasma metabolic phenotypes will be compared between groups at discharge and 12, 24 and 48 weeks post discharge. Briefly, global untargeted metabolomic phenotyping will be performed via ^1^H nuclear magnetic resonance (NMR) spectroscopy using a 700 MHz Bruker NMR spectrometer to identify metabolic signatures of SAM. Targeted analysis via ultra-performance liquid chromatography-mass spectrometry will be performed to examine specific pathways of interest, including tryptophan and bile acid metabolism.

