### Microbiota and metabolomics substudy

The primary comparison will be between HIV-negative children with oedematous and non-oedematous SAM, with a separate comparison between HIV-positive children with SAM and HIV-negative children with SAM. Analyses will examine (i) differences in metagenomic/metabolomic variables between groups at each time point; (ii) differences in metagenomic/metabolomic variables within groups over time; (iii) correlations between metagenomic and metabolomic variables and (iv) correlations between metagenomic/metabolomic variables and clinical outcomes. A systematic analysis will be undertaken to reduce high-dimensional data, integrate the multi-omics data sets and minimise false discovery.

Compositional metagenomic data will be compared between groups for indices of alpha and beta diversity. Principal coordinate analysis and partial least-squares discriminant analysis will be performed on metabolomics data to identify overall differences between groups. High-dimensional data sets will be reduced using random forest models to identify taxa, microbial gene families and metabolites that most strongly contribute to differences between groups, corrected by Benjamani-Hochburg false discovery rate detection. Targeted analysis by qRT-PCR will validate differential abundance or expression of candidate microbial genes. Longitudinal comparisons will be performed within and between groups using multilevel simultaneous component analysis. Orthogonal projections to latent structures models will integrate metabolomic and metagenomic data while linear regression, canonical correlation and hierarchal clustering analysis will measure correlations between -omics data sets. Finally, ROC analysis will identify the ability of different analytes to predict long-term nutritional and clinical outcomes.

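### The microbiota and metabolomics hypotheses claim independent association with in-hospital outcomes, but the only stated analysis linking these data to those outcomes is correlation, which cannot show independence.

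*Protocol article*

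**What the plan says.** All references are to the protocol article.

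**Hypotheses.** Under Substudies, Microbiota substudy, hypothesis (i) posits a microbial signature of HIV-SAM "that is independently associated with morbidity, mortality, nutritional recovery and degree of enteropathy during hospitalisation". Hypothesis (iii) says that "specific microorganisms or gut microbial diversity indices are independently associated with morbidity, mortality, nutritional recovery and degree of enteropathy during hospitalisation". Under Metabolomics substudy, hypothesis (i) posits a phenotype of oedematous SAM during hospitalisation, "which is independently associated with morbidity, mortality and nutritional recovery".

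**Analyses that link these data to outcomes.** The Microbiota substudy section says the sequencing data will be used "to investigate associative links between specific gut microbial signatures and clinical outcomes". Under Analysis, Microbiota and metabolomics substudy, the fourth listed aim is "correlations between metagenomic/metabolomic variables and clinical outcomes". The section closes by saying that "ROC analysis will identify the ability of different analytes to predict long-term nutritional and clinical outcomes". Its regression has another purpose: "linear regression, canonical correlation and hierarchal clustering analysis will measure correlations between -omics data sets".

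**Elsewhere in the article.** Under Analysis, Observational cohort, outcomes are analysed with multivariable Cox and linear models. Under Analysis, Immunology substudy, age, sex, oedema and baseline WHZ are added to the outcome models to examine confounding.

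**The concern.** An independent association is one that remains after other determinants of the outcome are accounted for. A correlation between a feature and an outcome does not account for them, so it answers a different question.

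The gap matters here because the confounders are part of the hypotheses. Microbiota hypothesis (i) expects features to differ by HIV status, and the Introduction reports that "inpatient deaths are almost fourfold higher among HIV-positive children with SAM" (30.4% v 8.4%). Metabolomics hypothesis (i) expects features to differ by oedema, and the Introduction says that the two forms of SAM differ in clinical outcome. A feature that only tags HIV or oedema would therefore be expected to correlate with death or slow recovery. Followed as written, the plan could report such a feature in support of a hypothesis that it has not tested.

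**Working it through.** **1. Which stated method addresses which question** (Analysis, Microbiota and metabolomics substudy)

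| Method | Stated use |
|---|---|
| Alpha and beta diversity, principal coordinates, PLS-DA, random forest | differences between groups |
| Multilevel simultaneous component analysis | longitudinal comparison within and between groups |
| Orthogonal projections, linear regression, canonical correlation, clustering | links between omics data sets |
| Correlations, aim (iv) | features v clinical outcomes |
| ROC | features v long-term outcomes |

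The three hypotheses above concern hospitalisation, so only the correlations reach them. The analysis of covariance under Sample sizes serves the sample-size estimate and does not reappear in the analysis section. The cohort's multivariable models do not fill the gap, because the risk factors named for them are clinical, demographic and routine laboratory variables.

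**2. How far an unadjusted correlation can mislead**

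Inputs: 100 HIV-positive and 100 HIV-negative children with SAM (Table 1); mortality 30.4% v 8.4% (Introduction), or 20% v 10% (assumed); a feature that differs by d SD between HIV groups (assumed, 0.3 to 1.0) and has no effect on death within either group.

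With equal groups, HIV alone induces this correlation between feature and death:

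- r(feature, HIV) = (d/2) / √(1 + d²/4)
- r(death, HIV) = ½(p₁ − p₀) / √(p̄(1 − p̄))
- r(feature, death) = the product of the two
- rejection rate ≈ P(|Z + r√200| > 1.96)

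At 30.4% v 8.4%, p̄ = 0.194 and r(death, HIV) = 0.11/0.3954 = 0.278. At 20% v 10%, p̄ = 0.15 and r(death, HIV) = 0.05/0.3571 = 0.140.

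Example, d = 0.5 at the first rates: r(feature, HIV) = 0.25/√1.0625 = 0.2425; r = 0.2425 × 0.278 = 0.0675; r√200 = 0.954; rejection rate ≈ 0.159.

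| d (SD) | r(feature, HIV) | Rejection, 30.4% v 8.4% | Rejection, 20% v 10% |
|---|---|---|---|
| 0.3 | 0.148 | 9% | 6% |
| 0.5 | 0.243 | 16% | 8% |
| 0.8 | 0.371 | 31% | 11% |
| 1.0 | 0.447 | 42% | 14% |

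Simulations agree. At 30.4% v 8.4%, separate runs gave about 9%, 15–17%, 29–31% and 42–44% for the four shifts. With HIV in the model the rate was about 5% (range 4.5% to 6%).

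**3. Does the planned false discovery control remove it?**

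No. It limits chance findings, and a confounded correlation is not a chance finding. With 200 features (assumed), half of them shifted by HIV and none affecting death, Benjamini-Hochberg on unadjusted correlations at 30.4% v 8.4% declared at least one feature in 29%, 64% and 79% of simulated studies (shifts 0.5, 0.8 and 1.0 SD), against 4–5% after adjustment for HIV. With 30% of features shifted, the range over 0.3 to 1.0 SD was about 10–66% at 30.4% v 8.4%, and about 8–17% at 20% v 10%. The rate per shifted feature was much lower: 0.1–9% and 0.1–0.5%.

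**4. Expected in-hospital deaths among 200 children**

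100 × 0.304 + 100 × 0.084 = 38.8; 100 × 0.20 + 100 × 0.10 = 30; at an assumed 10% overall, 200 × 0.10 = 20.

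**The case against.** The strongest reply is that an article condenses its plan. It points to a full protocol online, model form and covariates are commonly left to that document, and nothing says that the analyses will be unadjusted. The section also uses the word correlations loosely, since it lists regression among the methods that measure them. This disposes of any complaint about a missing covariate list. It does not dispose of the mismatch: the section names about ten methods with their purposes, none is an adjusted outcome model, and the same article commits to such models for the cohort and for immunology.

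The size is also open to challenge. The 30.4% v 8.4% is cited background, whereas the study's own planning mortality is 15% overall. The shifts are assumed, and false discovery control lowers the rate for each feature. The primary omics comparison lies within HIV-negative children, where HIV cannot confound. All of this stands and narrows the size. However, aim (iv) is not restricted to HIV-negative children, and oedema can confound within them, although that was not quantified.

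A reader might infer three stronger points, none of which the article supports:

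- **That the ROC analysis is single-analyte and is offered as proof of independence.** The text does not limit it to single analytes. It is planned for long-term outcomes, where the hypotheses speak of prediction, and ROC suits that.
- **That the second primary objective is at stake as a claim of independent pathogenic role.** That objective is to characterise pathogenesis better. Independent prediction belongs to the first objective, which has multivariable models. The article also says that all analyses are interpreted exploratively.
- **That oedema and baseline WHZ must always be adjusted for.** The article itself suggests that the microbiota may help cause SAM, so both may lie downstream of the feature.

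**Conclusion.** The point holds as a mismatch between stated hypotheses and stated analysis, limited to in-hospital morbidity, mortality and nutritional recovery in the microbiota and metabolomics substudies. Correlations alone cannot support the claim of independence in the three hypotheses.

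The size depends on assumptions. For HIV shifts of 0.3 to 1.0 SD, a nominal 5% test of a feature with no effect of its own rejects in about 9% to 44% of studies at the cited mortality rates and in about 6% to 14% at 20% v 10%, against about 5% after adjustment for HIV. These are nominal rates per feature with both HIV groups pooled. They illustrate the mechanism and do not forecast the study's error rate. No figure in the article is wrong on this point.

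**What to change.** Under Analysis, Microbiota and metabolomics substudy, aim (iv), state that the hypotheses of independent association will be tested with covariate-adjusted outcome regressions:

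- logistic or Cox models for death and morbidity, and linear or time-to-event models for nutritional recovery;
- age in every model, and HIV status wherever both HIV groups are pooled;
- oedema and baseline WHZ added, as the immunology substudy does, with results shown with and without them because they may be downstream;
- false discovery control applied to the adjusted p values;
- correlations kept as description.

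If this is not wanted, delete the word independently from the three hypotheses. That also resolves the mismatch.

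The cost is a change of wording, since HIV status, age, oedema and WHZ are already collected. The downside is statistical: with roughly 20 to 40 expected in-hospital deaths among 200 children, the models must stay small and fewer features will be declared.
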